### Updating

After external validation we will assess whether the predictive performance of the PIAMA model remains stable or improves by deleting or adding predictors that are available in the validation data.

By removing predictors, a more simple risk score will be created. The predictive performance of such a simple risk score will be compared with the predictive performance of the PIAMA Risk Score. A simpler risk score is preferable for application in practice
[17]. Potential additional predictors include e.g. child’s ethnicity, preterm birth, sleeping problems due to asthma symptoms, doctor visits due to asthma symptoms, wheezing patterns, allergy or general health. To study the prognostic value of additional predictors, we will refit the PIAMA Risk Score in the validation data and consequently add the new predictors. We will calculate the increase in AUC with 95% CI, and the p-value from the likelihood ratio test for improvement of goodness of fit. This will result in an updated PIAMA Risk Score. For optimal precision of the estimated coefficients, the updated PIAMA Risk Score will be fitted to the combined PIAMA and Generation R data.

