### Development of asthma risk appraisal tool

We will convert the updated PIAMA Risk Score to a computer-assisted tool, the so called ‘Asthma Risk Appraisal Tool’. The best cut-off scores of the Asthma Risk Appraisal Tool will be studied within the validation study. In an expert meeting we will discuss which decisions will follow the cut-offs: referral to general practitioner (=indirect referral to pediatrician)/ asthma nurse, extra consultation moment at well-child care, personal advise/counselling. The aim is to create an easy applicable (computer-assisted) tool for use of the PIAMA Risk Score in well-child care. A previous study developed a similar risk assessment tool to early detect children with global developmental disabilities in well-child care
[18]. A computer-assisted risk assessment tool heightens the uniformity of practice.

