### Sample size

At least 100 patients with the outcome and 100 without the outcome are needed for reliable external validation of a prediction model
[19].

Sample size at the age of 6 years: Assuming a prevalence of asthma of 5% at the age of 6 years (and it is known that 3967 children have ever had asthma symptoms at the age of 4 years) the Generation R study will have approximately 198 children aged 6 years
[19]. This implies that our effective sample size at the age of 6 years is sufficiently large for the primary aim of this study.

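### The updated PIAMA score is built, judged and given cut-offs in the same Generation R children with no optimism correction stated, so its reported performance would be modestly too good

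*Protocol article*

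**What the plan says.** The Updating section of the protocol article asks whether performance holds up or improves when predictors are dropped or added.

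- Removal: "The predictive performance of such a simple risk score will be compared with the predictive performance of the PIAMA Risk Score".
- Addition: "we will refit the PIAMA Risk Score in the validation data and consequently add the new predictors".
- Yardsticks: "We will calculate the increase in AUC with 95% CI, and the p-value from the likelihood ratio test for improvement of goodness of fit".
- Final fit: the coefficients of the updated score are estimated in the two cohorts combined, for precision.

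The section on developing the appraisal tool stays in the same data: "The best cut-off scores of the Asthma Risk Appraisal Tool will be studied within the validation study".

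The External validation section sets out calibration-in-the-large, calibration slope and C-index for the existing score. No matching assessment of the updated score in data it was not built on is described. The pilot counts children flagged as high risk and the actions taken; it does not compare predictions with observed asthma. The only internal validation mentioned is that of the original score (AUC 0.72, Background).

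The sample size is argued for validation alone: "At least 100 patients with the outcome and 100 without the outcome are needed for reliable external validation of a prediction model". Updating has no sample size argument of its own.

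**The concern.** Once the score is refitted in Generation R, that cohort is training data for the updated score. Three sources of optimism then add up:

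- **Refitting.** Adding a predictor to a nested model fitted by maximum likelihood cannot lower the log-likelihood, and it usually raises the AUC in the same children.
- **Selection.** The candidates form an open list, so those that look useful by chance are more likely to be kept.
- **Cut-offs.** A cut-off chosen as best in the same children looks better there than it will elsewhere.

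Nothing later in the study would reveal the bias. The pooled final fit uses both cohorts, the repeat at age 9 uses the same Generation R cohort, and the pilot has no outcome comparison. The Background itself holds that a model must be externally validated before it can be recommended for practice.

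At stake are the judgement on which predictors to keep, the risks that the tool gives, and the stated accuracy at the cut-offs to which the expert meeting will attach decisions.

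**Working it through.** **1. The plan's own figure.** The Sample size section gives the number of children ("it is known that 3967 children have ever had asthma symptoms at the age of 4 years") and the prevalence ("Assuming a prevalence of asthma of 5% at the age of 6 years"). 3967 × 0.05 = 198.35, which reproduces the stated 198.

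**2. A lower scenario.** The last response rate listed under Design and setting, read as that at age 6, is 68%. Assuming it applies to the symptomatic children, 3967 × 0.68 = 2697.6, about 2698 children, and 2698 × 0.05 = 134.9, about 135 events.

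**3. Parameters.** Of the eight PIAMA predictors, one has no replacement in Generation R and one has a proxy, leaving 7. Seven new candidates are named by way of example. I take 7 or 14 added parameters, because several candidates may have more than two categories.

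| Events | 7 + 7 = 14 parameters | 7 + 14 = 21 parameters |
|---|---|---|
| 198 | 198/14 = 14.1 per parameter | 198/21 = 9.4 |
| 135 | 135/14 = 9.6 | 135/21 = 6.4 |

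**4. Chance that at least one useless predictor passes p<0.05.** With k independent tests this is 1 − 0.95^k: 0.302 for k = 7 and 0.512 for k = 14.

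**5. Size of the optimism.** The documents give no figure, so it was simulated. Assumptions: logistic model, 5% prevalence, 7 normally distributed base predictors with AUC near 0.72, and candidates with no true effect. Each candidate was kept if its likelihood ratio test against the refitted base gave p<0.05, and the cut-off maximised sensitivity + specificity − 1. There were 120 replicates per scenario, and truth was evaluated in 100,000 new children. Optimism is apparent minus new, from unrounded values.

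| Children (events) | Null candidates | Base AUC, apparent / new | Updated AUC, apparent / new | AUC optimism | Apparent gain | True change | Cut-off optimism |
|---|---|---|---|---|---|---|---|
| 3967 (198) | 7 | 0.719 / 0.710 | 0.721 / 0.708 | 0.012 | +0.0014 | −0.0014 | 0.042 |
| 3967 (198) | 14 | 0.724 / 0.711 | 0.727 / 0.708 | 0.019 | +0.0026 | −0.0023 | 0.053 |
| 2698 (135) | 7 | 0.721 / 0.703 | 0.724 / 0.701 | 0.023 | +0.0026 | −0.0024 | 0.067 |
| 2698 (135) | 14 | 0.723 / 0.713 | 0.726 / 0.710 | 0.017 | +0.0035 | −0.0033 | 0.051 |

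At least one useless predictor entered in 32% to 47% of data sets. If all candidates are added without selection, AUC optimism is 0.020 to 0.038, the apparent gain is 0.005 to 0.014 against a true loss of 0.005 to 0.013, and the calibration slope in new children is 0.82 to 0.90. That slope belongs to the all-candidates model; it was not computed for the selected one.

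The base model's optimism moves between 0.009 and 0.018 without a clear pattern, partly from simulation noise, so the third decimal should not be relied on.

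**6. A different set-up.** Binary predictors with prevalence 0.25, forward selection at p<0.05 and a weaker base model:

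- 2698 children: apparent AUC 0.686 against a true 0.659 to 0.660, optimism about 0.026. Apparent gains of +0.0035 (7 candidates) and +0.0048 (12) were true changes of −0.0026 and −0.0044.
- 3967 children: 0.682 against 0.665, optimism 0.017.

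The two set-ups agree in direction and order of size.

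**The case against.** **The article is condensed.** A bootstrap or shrinkage step could stand in a fuller plan that is not shown, and the article nowhere says that performance will go uncorrected. This limits the point but does not remove it: the article itself fixes the data, the order of steps and the measures, and those steps as written yield apparent performance.

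**Added predictors are not compared with the externally applied score.** A reader might infer that the original score is judged externally and the extended score in-sample, so that the extension wins by construction. The text does not support this. The PIAMA score is refitted first, and the gain is measured against that refitted model. Both sides are in-sample, and the bias in the gain is far smaller than the total optimism.

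**The simplified score need not be flattered.** A reader might infer that it will look as good as the original when it is not. That requires the reduced score to be refitted and the original not, and the article does not say which is done. If both are refitted, the fuller model carries more optimism; if neither is, there is no optimism from refitting. If only the reduced score is refitted, the comparison tilts: in a simulation, refitting alone, set against exactly true coefficients, seemed to gain 0.005 to 0.008 AUC and truly lost 0.004 to 0.007.

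**The planned confidence interval and test give some protection.** A likelihood ratio test of one prespecified addition is valid. The difficulty is choosing from an open list and then reporting performance in the same children. Nor will useless predictors always seem to help: in these simulations none entered in more than half of the data sets.

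**Assumptions and pooling.** Null candidates are a worst case; doctor visits or sleep disturbed by symptoms may well be predictive. The selection rule and the cut-off criterion are not in the article. Pooling with PIAMA should reduce overfitting of the final coefficients, and the simulations do not represent that fit. These objections stand as limits on the size, not on the direction.

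**Conclusion.** The point holds in a modest form. As written, the plan would report AUC, AUC gain, calibration and cut-off performance of the updated score from data used to build it, and neither cohort named in the article remains independent of it.

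With about 135 to 198 events, null candidates and p<0.05 selection, AUC optimism is about 0.01 to 0.03. An apparent gain of 0.001 to 0.005 can be a small true loss, so the bias matters mainly when small gains decide which predictors are kept. The optimism in sensitivity + specificity − 1 of about 0.04 to 0.07 also assumes that the cut-off is chosen to maximise that sum.

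The external validation of the unmodified score, which the sample size serves, is not affected. A reader might infer that the pilot tool will carry badly overstated risks; the documents do not support that, since the final coefficients come from the pooled data and their optimism has not been quantified. This is a recommended correction to make before updating begins, not a flaw that undermines the study.

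**What to change.** State in the Updating section that the whole procedure (removal, addition, refit and choice of cut-off) will be repeated in bootstrap samples. Because the final coefficients come from the pooled fit, that fit should be inside the loop too. Then:

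- compare the original, simplified and extended scores on the same footing, saying which are refitted, with the optimism-corrected C-index and calibration slope;
- shrink the final coefficients if the corrected slope is below 1;
- report optimism-corrected performance at the chosen cut-offs.

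The cost is some programming and a slightly less favourable reported AUC; no new data are needed. A net-benefit analysis, or holding the expert meeting before cut-offs are studied, is optional and not part of this correction.

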### Asthma outcomes

The outcome that is predicted with the PIAMA Risk Score is asthma at school age. In the development study (PIAMA) the following 3 items were used for the case definition of asthma: (1) at least 1 episode of wheezing in the last 12 months; (2) inhaled steroids prescribed by a medical doctor in the last 12 months; and (3) a doctor’s diagnosis of asthma (a parental report of a doctor’s diagnosis of asthma at any time and a parental report of asthma in the last 12 months). In the analyses children were only considered positive for asthma if they had 1 or more positive items at age 7 years and 1 or more positive items at age 8 years
[7].

Within the validation data (Generation R), we aim to use the same asthma definition as used in PIAMA and we aim to select only children with ‘active asthma’ or clinically relevant chronic asthma symptoms. First, we will define asthma at the age of 6 years in the children who have ever had reported asthma symptoms before the age of 4 years. Additionally, the analyses will be repeated in children at age 9 years. At age 9 years spirometry will be performed in children at the research center. Spirometry is used to improve the accuracy of an asthma diagnoses and will be enable us to compare asthma outcomes based on parental reports to asthma outcomes based on spirometry.

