### Preschool predictors

The eight predictor variables used in the PIAMA Risk Score are: 1) sex, 2) post-term delivery, 3) parental education, 4) parental inhalation medication, 5) child’s wheezing frequency, 6) wheezing/dyspnea apart from colds, 7) serious infections and 8) doctor’s diagnosis of eczema and eczematous rash present. The variables wheezing/dyspnea apart from colds and parental inhalation medication are not available within the Generation R Study at preschool age. For parental inhalation medication a proxy variable of parental asthma is available. Information on sex and pregnancy duration are obtained from medical records; parental education and asthma are established using questionnaires during pregnancy; wheezing frequency, respiratory tract infections and eczema are measured using questionnaires at the ages of 1, 2, 3 and 4 years.

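### The updated score is to be fitted to PIAMA and Generation R pooled, with no stated cohort term or recalibration, although outcome timing and one predictor differ; if baseline risk differs, its absolute risks would be misstated

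*Protocol article*

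**What the plan says.** All references are to Methods and design in the protocol article.

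- **Updating.** Predictors are deleted, or added from those available in the validation data, with the score refitted in Generation R. The last step, justified by the precision of the coefficients, is that "the updated PIAMA Risk Score will be fitted to the combined PIAMA and Generation R data".
- **Asthma outcomes, PIAMA.** Children counted as cases "if they had 1 or more positive items at age 7 years and 1 or more positive items at age 8 years".
- **Asthma outcomes, Generation R.** The intention is stated as "we aim to use the same asthma definition as used in PIAMA and we aim to select only children with" active disease or clinically relevant chronic symptoms. The timing is then set: "First, we will define asthma at the age of 6 years in the children who have ever had reported asthma symptoms", and "Additionally, the analyses will be repeated in children at age 9 years".
- **Preschool predictors.** Two of the eight PIAMA predictors were not collected in Generation R at preschool age. For one of them, "For parental inhalation medication a proxy variable of parental asthma is available". No substitute is named for wheezing or dyspnea apart from colds.
- **External validation.** Predictor and outcome distributions and odds ratios are compared between the cohorts. Calibration-in-the-large and calibration slope are assessed for predictions from the PIAMA score.
- **Development of asthma risk appraisal tool.** The updated score becomes the tool, and its cut-offs are studied within the validation study.

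**The concern.** Pooling improves precision when both cohorts estimate the same quantity. Here the outcome is positivity at two ages in one cohort and at a single, different age in the other. One predictor is medication use in one cohort and parental disease in the other. The Discussion expects few differences in design and analysis between the studies, which sits uneasily with these sections.

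A logistic model fitted to stacked data with no cohort term gives both cohorts one intercept. Any difference in risk not explained by the predictors then goes to two places: an averaged intercept, and the coefficients of predictors whose distribution differs by cohort. Ethnicity, one of the candidate additions, could be such a predictor, since Generation R is multi-ethnic.

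The planned comparability and calibration checks could reveal such a difference, but the article does not say that they bear on whether or how to pool. The calibration checks are described for the PIAMA score, not for the pooled model. At stake are the absolute risks of the model behind the tool, and possibly some of its weights.

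**Working it through.** **1. The plan's own figure.** Sample size takes 3967 children with symptoms and an assumed asthma prevalence of 5% at age 6: 3967 × 0.05 = 198.35, which matches the stated 198. These are the Generation R inputs below.

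**2. What is not in the document.** No PIAMA sample size or prevalence is given. Both are assumed here: size 1000 to 4000, prevalence 3% to 15%.

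**3. Common intercept, no cohort term.** Suppose the cohorts have the same predictor distribution, so that the whole prevalence difference is a difference in baseline risk. Ignoring the spread of the predictors for now:

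- pooled prevalence = (n_G × p_G + n_P × p_P) / (n_G + n_P), with G for Generation R and P for PIAMA
- expected/observed (E/O) in a cohort = pooled prevalence / cohort prevalence
- intercept error in a cohort = logit(cohort prevalence) − logit(pooled prevalence)

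Example, PIAMA 2000 children at 11%: (198.35 + 220) / 5967 = 0.0701. E/O is 0.0701/0.05 = 1.40 in Generation R and 0.0701/0.11 = 0.64 in PIAMA. The intercept errors are −0.36 and +0.49.

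| Assumed PIAMA n | Assumed PIAMA prevalence | Pooled prevalence | E/O Generation R | E/O PIAMA |
|---|---|---|---|---|
| 2000 | 3% | 4.33% | 0.87 | 1.44 |
| 2000 | 5% | 5.00% | 1.00 | 1.00 |
| 2000 | 8% | 6.01% | 1.20 | 0.75 |
| 2000 | 11% | 7.01% | 1.40 | 0.64 |
| 2000 | 15% | 8.35% | 1.67 | 0.56 |
| 1000 | 8% | 5.60% | 1.12 | 0.70 |
| 1000 | 15% | 7.01% | 1.40 | 0.47 |
| 4000 | 8% | 6.51% | 1.30 | 0.81 |
| 4000 | 15% | 10.02% | 2.00 | 0.67 |

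For 8% to 15% and 1000 to 4000 children, E/O is 1.12 to 2.00 in Generation R and 0.47 to 0.81 in PIAMA. The error reverses at 3% and is zero at 5%.

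**4. With a predictor in the model.** A large-sample logistic simulation used equal slopes in both cohorts, a linear predictor with SD 0.82 (about the AUC of 0.72 quoted in Background) and cohort sizes in the ratio 3967 to 2000. With PIAMA at 11% and no cohort term, calibration-in-the-large was −0.38 in Generation R (E/O 1.40) and +0.53 in PIAMA (E/O 0.64), in line with step 3.

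**5. With a cohort-specific intercept.** In the same simulation, calibration-in-the-large was 0.00 and E/O 1.00 in both cohorts at each PIAMA prevalence tried (5%, 8%, 11%, 15%), with the slope about 1.01.

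**6. What this does not show.** The simulated predictor was unrelated to cohort, so the runs do not measure distortion of coefficients related to cohort. That part rests on the usual argument about an omitted variable: if cohort affects risk and is left out, predictors associated with cohort take up part of its effect.

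**The case against.** - **A common intercept is not written down.** The article neither states nor excludes a cohort term, and a condensed article may leave the model specification to a fuller plan. This stands, so the missing term alone is weak evidence of an error. But the pooled fit, and precision as its reason, are stated choices that can be commented on.
- **A difference in prevalence is not documented.** A reader might infer that the pooled model will be calibrated in neither cohort. The document does not support this: only the assumed 5% for Generation R is given, and the error is zero if baseline risk is equal. Even different crude prevalences would not be enough if the predictors explained them. The figures above place the whole difference in the intercept by assumption.
- **The outcome items are meant to be the same.** This stands. What differs is age and the two-age rule. Because the ages differ too, the direction of any difference in risk cannot be derived.
- **Cut-offs are studied in the validation study.** A reader might infer that an intercept error changes which children are labelled high-risk. It does not follow: a pure shift leaves the ranking unchanged, and a score cut-off chosen in Generation R selects the same children. Only distorted coefficients could change the ranking.
- **A predictor absent from Generation R is not being pooled.** Wheezing or dyspnea apart from colds cannot be in a score refitted in Generation R. Whether any added predictor is missing from PIAMA is not stated.
- **Pooling regardless of results is not stated either.** Updating follows external validation, so its results will be known. What is absent is any rule connecting them to the pooled fit.

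**Conclusion.** The point holds in conditional form. The article commits to a pooled fit for precision and does not say how differences between the cohorts will be handled, although its own sections show different outcome timing and a proxy for one predictor. If baseline risk given the predictors differs and no cohort term is used, absolute risks will be wrong for Generation R in one direction and for PIAMA in the other.

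The size is unknown. The ranges in the working depend on assumed PIAMA figures, a single intercept, and a prevalence difference that lies wholly in baseline risk. They show that the error could be anything from none to a doubling of predicted risk in Generation R, and could also be an understatement.

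The external validation of the existing PIAMA score is unaffected. This is an inexpensive improvement to the final modelling step, not a flaw in the study's main aim.

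**What to change.** In Updating, specify that:

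1. the pooled model includes a cohort indicator, and the tool is issued with the intercept for the Generation R outcome;
2. coefficients are pooled only for predictors measured comparably in both cohorts, and only where the odds-ratio comparison in External validation shows them to be consistent;
3. the parental-asthma proxy, and any added predictor measured only in Generation R, is estimated in Generation R, for example with the pooled part of the linear predictor as an offset.

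Fitting in one cohort and testing in the other before the final fit would be a useful addition but is optional.

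The cost is a few model terms and a small loss of precision for coefficients that are not pooled. No further data are needed.

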### Subgroup analysis

The PIAMA Risk Score was developed within a general population. However, it is known that children of ethnic minorities and children with low socioeconomic status are at high risk of developing asthma. Within well-child care it is important to give attention to high risk groups. Therefore, it is important to test the predictive ability of the PIAMA Risk Score in both the general population and in specific subgroups (e.g. at different ages or in children of ethnic minorities and children with low socioeconomic status).

